### Monitoring

The effectiveness and safety of the treatment will be evaluated by an independent reviewer annually. The monitoring committee will monitor the trial’s safety, adherence to protocol, and progress and will modify the protocol as necessary and determine the need for early termination of treatment.

### Statistical Analysis

The 2-stage minimax design of Simon was chosen for sample size estimation. With an ORR of 17% or less, HIFU with PD-1 blocking as a combination therapy will be deemed useless or uninteresting; With an ORR of at least 37%, this regimen will warrant further investigation. At a significance level of .05, an analysis with 80% power will require a sample size of at least 30 patients, with 14 during the initial phase and 16 in the next. At the end of the first stage, if 2 or more patients have responded, the second stage can be carried out. If this does not happen, the study has to end. At the end of the study, if at least 8 of 30 patients respond, it will be taken to indicate that the combination therapy is beneficial and worthy of further investigation.

In accordance with the concept of “intention to treat,” all individuals who are given a minimum of 1 injection of the trial medication and undergo effectiveness assessment will be included in efficacy analyses. All patients who are injected with a minimum of 1 dose of the research medication and have a minimum of 1 safety report will be included in the safety analysis. Once we have recorded baseline features, tumor responses, patient-reported outcomes, and adverse events, we will produce descriptive statistics, including Kaplan-Meier survival curves. There will be no data imputation for missing data.

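### The Simon rule as stated (at least 2 of 14, then at least 8 of 30) has a type I error of 12%, not the stated 5%

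*Protocol article*

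**What the plan says.** Everything needed is in one paragraph of the protocol article, Methods, Statistical Analysis.

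- Design: "The 2-stage minimax design of Simon was chosen for sample size estimation".
- Null rate: "With an ORR of 17% or less, HIFU with PD-1 blocking as a combination therapy will be deemed useless or uninteresting".
- Target rate: "With an ORR of at least 37%, this regimen will warrant further investigation".
- Error rates and size: "At a significance level of .05, an analysis with 80% power will require a sample size of at least 30 patients", split into 14 and then 16.
- Stage 1: "if 2 or more patients have responded, the second stage can be carried out"; otherwise the trial must end, so the stop is binding.
- Final decision: "if at least 8 of 30 patients respond, it will be taken to indicate that the combination therapy is beneficial" and deserves further study.

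No other section gives a different cut-off or a more lenient significance level.

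**The concern.** In Simon's notation a design is listed by r1 and r, and the regimen passes a stage only when responses **exceed** the bound. A success threshold of 8 in 30 is 26.7%, which looks low for rejecting a 17% rate at the 5% level. It is what one would see if r = 8 had been read as the number needed rather than the number to exceed.

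The trial has one arm and response rate is its primary end point, so this threshold is the whole efficacy decision. If its error rate is wrong, the chance of taking an inactive combination forward is not the one that the plan declares.

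**Working it through.** **Inputs** (all from Statistical Analysis): p0 = 0.17, p1 = 0.37, n1 = 14, n2 = 16, continue if X1 ≥ 2, success if X1 + X2 ≥ 8. Sidedness is not stated. A Simon test is one-sided by construction, so .05 is taken as one-sided.

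**Formula.** The probability of declaring success at true rate p is

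Σ (x = 2 to 14) C(14, x) p^x (1 − p)^(14 − x) × P[Bin(16, p) ≥ 8 − x].

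**Step 1: type I error, p = 0.17.**

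| X1 | P(X1) | P(X2 ≥ 8 − X1) | Product |
|---|---|---|---|
| 2 | 0.2811 | 0.0412 | 0.0116 |
| 3 | 0.2303 | 0.1211 | 0.0279 |
| 4 | 0.1297 | 0.2836 | 0.0368 |
| 5 | 0.0531 | 0.5277 | 0.0280 |
| 6 | 0.0163 | 0.7830 | 0.0128 |
| 7 | 0.0038 | 0.9493 | 0.0036 |
| ≥ 8 | 0.0008 | 1 | 0.0008 |

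The sum is **0.1215**. The stated value is .05, and 0.1215 / 0.05 = 2.43.

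**Step 2: power, p = 0.37.** The same sum gives **0.911**, against the stated 80%.

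**Step 3: stage 1.** P(X1 ≤ 1) is 0.0736 + 0.2112 = 0.2848 at 17%, so the interim rule stops an inactive regimen 28.5% of the time. At 37% it stops 1.4% of the time.

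**Step 4: can another reading recover .05?**

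- Ignoring the early stop (single stage, at least 8 of 30): type I error 0.124, power 0.916.
- Reading .05 as two-sided (one-sided .025): the gap widens, and the minimax total becomes 38.
- Reading both cut-offs as bounds to exceed (at least 3 of 14, at least 9 of 30): 0.0526 and 0.816. This is close, but still above .05.
- A lower null rate: the rule gives 4.9% at 14% and 6.8% at 15%, and crosses 5% just below 14.1%. The plan fixes 17%.

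**Step 5: other cut-offs with 14 then 30 patients.**

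| Continue | Success | Type I error | Power |
|---|---|---|---|
| ≥ 2 | ≥ 8 | 0.1215 | 0.911 |
| ≥ 2 | ≥ 9 | 0.0558 | 0.834 |
| ≥ 3 | ≥ 9 | 0.0526 | 0.816 |
| ≥ 4 | ≥ 9 | 0.0431 | 0.750 |
| ≥ 2 | ≥ 10 | 0.0223 | 0.722 |

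A search over all cut-off pairs at 14/30 finds none with type I error ≤ .05 and power ≥ .80.

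**Step 6: is it minimax?** A search over total size, stage-1 size and cut-offs finds no feasible design below 29 patients. At 29, the design with the smallest expected size under the null is 17 in stage 1, continue at ≥ 3, success at ≥ 9 (0.0458, 0.801). The stated total of 30 is one patient away from this, but the split and cut-offs are not those of a minimax design.

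**The case against.** The arithmetic is not in dispute, but several points limit its weight.

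- **It is a phase 2 screen.** A positive result leads to further study, not to a claim of efficacy, and the Discussion concedes the small sample and the single arm. This stands. It limits the harm of a false positive, but it does not make 12% equal to 5%.
- **Power is better than stated.** This also stands: the rule errs toward false positives and does not miss effects. A sponsor could choose that trade-off, but the plan would then have to declare it.
- **The minimax label is minor.** Agreed. A total of 30 against 29 is immaterial; the cut-off is the fault.
- **The off-by-one explanation is a conjecture.** Agreed. It fits well (0.0526, 0.816) but cannot be proved from the text, and nothing here depends on it.
- **The confidence interval proves nothing.** The exact two-sided 95% interval at 8/30 (12.3% to 45.9%) contains 17%, but so does the interval at 9/30 (14.7% to 49.4%). It does not separate the faulty rule from a sound one, so it is not used as evidence.
- **Stage 1 may not be untouched.** The Results section reports 6 recruits by April 2024, fewer than 14, but later enrolment is unknown. The Monitoring section has effectiveness reviewed every year. Whether responses are already known must be confirmed, not assumed.

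**Conclusion.** The concern holds and must be fixed. The paragraph contradicts itself: its decision rule has a type I error of 12.15% at the 17% null, not 5%, and power of 91.1% at 37%, not 80%. An inactive regimen would be declared beneficial about one time in eight instead of one in twenty. The result is exact and uses only the plan's own inputs. It assumes a one-sided .05, a binding early stop and 30 evaluated patients; dropping the stop or reading .05 as two-sided does not rescue the stated level. An analysis plan that keeps these inputs could not make 8 of 30 consistent with 5%.

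**What to change.** Remove the 8-of-30 rule, adopt one of the designs below, and state its exact type I error and power, with the level given as one-sided.

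| Design | Continue | Success | Type I error | Power | Stops at stage 1 if 17% | Stops at stage 1 if 37% |
|---|---|---|---|---|---|---|
| A: true minimax | ≥ 3 of 17 | ≥ 9 of 29 | 0.0458 | 0.801 | 42.9% | about 2% |
| B: keep 30 patients | ≥ 4 of 16 | ≥ 9 of 30 | 0.0499 | 0.801 | 71.6% | 10.2% |
| C: keep the stage-1 rule | ≥ 2 of 14 | ≥ 9 of 29 | 0.0458 | 0.801 | 28.5% | 1.4% |
| D: keep 14 then 30 | ≥ 3 of 14 | ≥ 9 of 30 | 0.0526 | 0.816 | 56.6% | 6.3% |

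A matches the design that the plan names. B meets .05 by only 0.0001 and, of the four, is the most likely to stop an active regimen early. C leaves the interim rule as it is, so it is the safest choice if stage-1 responses are already known. D is acceptable only if the plan states 0.053 rather than .05.

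The amendment should record how many patients were enrolled on its date and that no response data informed the choice.

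**Cost:** a short change to the statistics section and no extra patients. The success threshold rises from 8 to 9 responders, the stage-1 threshold also rises under A, B and D, and power falls from 91.1% to between 80% and 82%, about the level that the plan already claims.

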**Methods:**

The HILL study is a single-armed, single-center, phase 2 clinical trial that will enroll 30 patients with lung cancer and liver metastases. The treatment regimen involves administering HIFU to liver metastases 1 week before the first dose of a programmed cell death protein (PD)–1 blockade, which is then administered every 3 weeks. The primary aim is to determine the overall response rate based on immune-related response criteria. Secondary aims include safety, progression-free survival, overall response, overall survival, and quality of life. Exploratory studies will also be conducted using whole blood, plasma, archival cancer tissue, and tumor biopsies during progression or relapse to identify potential biomarkers.

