### End Points

Overall response rate (ORR) is the primary end point. The secondary end points are PFS, OS, disease control rate, safety, and patient-reported outcomes, including the results of the European Organization for Research and Treatment of Cancer Quality of Life Questionnaire–Core 30 and Quality of Life Questionnaire–Lung Cancer Module 13. MRI or CT examinations will be administered at the start point, week 3, and each 6 weeks following. According to the RECIST1.1 and the National Cancer Institute Common Terminology Criteria for Adverse Events (version 5.0), tumor response and adverse events will be evaluated and recorded during therapy and within 28 days after the last dose, respectively. Telephone checks will be conducted every 3 months until the end of the trial, death, or loss to follow-up.

After illness progression or withdrawal from the trial’s treatment, the use of anticancer medication will be recorded. ORR is the proportion of enrolled patients with a CR or PR based on imaging. PFS is the length of time between enrollment and the occurrence of disease progression. OS is the duration between enrollment and death.

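### The primary ORR has two denominators: enrolled patients under End Points, but only injected and assessed patients, mislabelled intention to treat, under Statistical Analysis

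*Protocol article*

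**What the plan says.** Three statements in the protocol article bear on who is counted in the primary result.

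- Methods, End Points: "ORR is the proportion of enrolled patients with a CR or PR based on imaging".
- Methods, Statistical Analysis, introduced as following the intention-to-treat concept: "all individuals who are given a minimum of 1 injection of the trial medication and undergo effectiveness assessment will be included in efficacy analyses".
- The same section, on missing values: "There will be no data imputation for missing data".

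Two timing statements determine who can fall between the first two. The Abstract (Methods) describes "administering HIFU to liver metastases 1 week before the first dose" of PD-1 blockade; the Intervention section allows no more than 7 days between the two. For imaging, End Points states: "MRI or CT examinations will be administered at the start point, week 3, and each 6 weeks following".

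The Simon design in Statistical Analysis uses 14 patients in stage 1 and 16 in stage 2. It continues with 2 or more responders and is positive with at least 8 of 30. The Abstract says that 30 patients will be enrolled. The article does not say whether patients outside the efficacy set are replaced.

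**The concern.** One primary endpoint has two denominators, and a fuller analysis plan could follow only one of them. The second is not intention to treat: requiring both an injection and an assessment makes it a response-evaluable set.

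The patients on whom the two differ are not a random subset. Ablation comes first, then the first PD-1 dose, then the first post-baseline scan at week 3. Someone who is enrolled or ablated and then has a complication, deteriorates, dies or withdraws before the dose or the scan counts under End Points but not under Statistical Analysis. Removing early failures pushes the ORR up.

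In a single-arm trial judged against a fixed 17%, no control group undergoes the same exclusions, so nothing offsets the bias. It is also unclear which patients make up the 14 and the 30.

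**Working it through.** **Inputs.** From Statistical Analysis: uninteresting ORR p0 = 0.17, target ORR p1 = 0.37, stages of 14 and 16, cutoffs of at least 2 of 14 and at least 8 of 30, stated significance level .05 and power 80% (taken as one-sided, since sidedness is not given). From the Abstract: 30 enrolled. Not in the article, and so assumed: the share d of enrolled patients who fall outside the efficacy set, and that those patients are non-responders. The second assumption is certain for anyone never scanned. For a patient never injected it means no response credited to ablation alone.

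**1. The plan's own figures.** With X1 ~ Bin(14, p) and X2 ~ Bin(16, p),

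P(positive) = Σ (x = 2 to 14) P(X1 = x) · P(X2 ≥ 8 − x).

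At p = 0.17 this is 0.1215; at p = 0.37 it is 0.911. The stated .05 and 80% are therefore not reproduced by the stated cutoffs. That is a separate error. It matters here only because 12.1% is the starting point in step 3.

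**2. Reported ORR, 30 enrolled, no replacement.** With 8 responders and k patients dropped, the reported ORR is 8/(30 − k).

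| Dropped (k) | Denominator | Reported ORR |
|---|---|---|
| 0 | 30 | 26.7% |
| 1 | 29 | 27.6% |
| 2 | 28 | 28.6% |
| 3 | 27 | 29.6% |
| 4 | 26 | 30.8% |
| 5 | 25 | 32.0% |

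The number of responders stays at 8 in every row. Dropping non-responders cannot turn 7 responders into 8, so the count-based decision is the same on either denominator. The percentage and its confidence interval move.

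**3. Decision rule, only if patients are replaced until 30 are evaluable.** If the true ORR in enrolled patients is 0.17 and a share d is removed, the rate among evaluable patients is 0.17/(1 − d). Putting this into the formula of step 1:

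| d (assumed) | Evaluable ORR | P(positive), stated cutoffs |
|---|---|---|
| 0 | 17.0% | 12.1% |
| 10% | 18.9% | 18.9% |
| 15% | 20.0% | 23.5% |
| 20% | 21.3% | 29.2% |

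To separate this from the cutoff error, take for illustration a rule that is not in the article but does hold the level: at least 4 of 16, then at least 9 of 30 (exact level 0.0499, power 0.801). The same three exclusion rates move it from 5.0% to 8.7%, 11.5% and 15.3%. The relative effect of replacement is therefore not an artefact of the cutoffs.

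**The case against.** The strongest objection concerns the decision rule. A reader might infer that the present efficacy set by itself raises the false-positive rate of the Simon design. The article does not support that. The rule counts responders, no section provides for replacement, and the Abstract's plan to enroll 30 reads against it, although the Statistical Analysis section's wording of at least 30 leaves some room. Without replacement, step 3 does not apply. This objection stands, and the false-positive figures are conditional on replacement.

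Second, the exclusion rates are assumed, and the text suggests that they may be low. Eligibility excludes a life expectancy of 3 months or less and requires ECOG 0-2, and only failures before about the first scan are lost. With one or two exclusions the ORR moves from 26.7% to 27.6% or 28.6%. This stands as a limit on size; it does not remove the conflict.

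Third, a reader might take the no-imputation sentence as a settled policy never to count unassessed patients as non-responders. It does not say so. Classing an unassessed patient as a non-responder is an endpoint rule, not imputation, and the enrolled-patient definition already implies it. What removes these patients is the definition of the efficacy set. Detailed handling of non-evaluable patients may well sit in a plan not shown, but such a plan cannot satisfy two incompatible published denominators.

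**Conclusion.** The concern holds as a contradiction in the definition of the primary analysis, with a mislabelled analysis set. The direction is clear, given that excluded patients are non-responders: the reported ORR is too high, or unchanged if nobody is excluded. The size is unknown because the article gives no exclusion rate. Over an assumed 1 to 5 exclusions among 30 it is about 1 to 5 percentage points on an ORR of 26.7%.

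Error inflation in the go/no-go decision is a possibility that the article leaves open, not something it lays down. It arises only with replacement, and the 12.1% from which it starts belongs to the separate problem with the cutoffs.

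The point should be settled before the stage 1 look at 14 patients. The article reports 6 recruited by April 2024.

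**What to change.** - Define the primary ORR set as all enrolled patients, in line with End Points, and count anyone without a post-baseline assessment as a non-responder. A set of all who start HIFU would be a third denominator and would still depart from that definition.
- Apply the stage 1 and final Simon counts to that set, and state that patients are not replaced.
- Keep the injected-and-assessed set as a secondary analysis, labelled response-evaluable, and drop the intention-to-treat label from it.
- State that the 17% and 37% refer to enrolled patients.

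**Cost.** The change is one of wording, and the reported ORR may be slightly lower. Power is affected only if the 37% was meant for evaluable patients. With an assumed 15% unassessed, the enrolled rate would then be 0.37 × 0.85 = 31.5%, and exact power under the stated cutoffs would fall from 91.1% to 76.6% (from 80.1% to 59.4% under the illustrative rule that holds the level). If the 37% already refers to enrolled patients, nothing is lost, which is why the plan should say so.

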**Objective:**

We designed the HILL (Ultrasound-Guided High-Intensity Focused Ultrasound Combined With PD-1 Blockade in Patients With Liver Metastases From Lung Cancer) study to investigate the effectiveness and safety of HIFU in combination with immunotherapy for lung cancer with liver metastases.

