### Intervention

Eligible patients will receive HIFU on liver metastases and PD-1 blockade therapy. Given the potential immunomodulation effect of HIFU, ablation of metastatic liver lesions was planned to take place within no more than 7 days of immunotherapy. The PD-1 blockade was injected repeatedly every 3 weeks for 6 cycles. The combination of immunotherapy and ablation was administered once in week 1. The study schema provides a comprehensive summary (Figure 2). Patients who are considered to have obtained clinical benefits, including a complete response (CR), partial response (PR), or having achieved stable disease (SD), will be allowed to continue PD-1–blocking medicines (every 3 weeks) for up to 2 years beyond the end of the trial. Patients with progressive disease will exit the trial or undergo re-ablation with HIFU according to their choice. Re-ablation will be performed in liver metastases without changing the immunotherapy regimen, and the efficacy will be evaluated 3 weeks later. If the treatment outcome is progressive disease, the patient will be withdrawn from the study. If the outcome is SD, PR, or CR, the patient will be treated and followed up. The standard PD-1 blockade treatment plan for advanced lung cancer with liver metastases will be used, as determined by the investigators and based on clinical guidelines.

Whole blood, plasma, archived cancer tissue, and tumor biopsies will be taken for exploratory research. Given the stability and availability of the test, peripheral blood will be obtained for lymphocyte subsets and the levels of 12 cytokines (tumor necrosis factor [TNF]-α, interleukin [IL]-6, IL-10, IL-17, interferon [IFN]-α, IL-1β, IL-2, IL-5, IL-8, IL-12P70, IFN-γ, IL-4) will be measured before and after HIFU treatment. Tumor biopsy tissue will be embedded in paraffin and analyzed for immune cell infiltration and PD-L1 expression. This information will help us determine whether the medication modifies the diversity of immune response and whether these changes are reflected in the blood. This could aid in the selection of predictive biomarkers for patients in future trials by connecting immunological alterations to clinical symptoms.

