### Focused Ultrasound Ablation

Patients were chosen according to the following HIFU treatment inclusion criteria: (1) suitability for anesthesia and sedation, (2) visibility in diagnostic sonography, (3) accessibility (maximum of 11 cm between the skin and the deepest tumor sections), (4) absence of extensive scarring or extensive calcifications along the acoustic route, and (5) absence of metal clips following surgery. Ultrasound-guided HIFU will be performed with a HIFU system (the Focused Ultrasound Tumor Therapeutic System [model-JC200]; Chongqing Haifu Medical Technology Co Ltd), with the patient in a lateral position. Operational details were chosen with reference to previous studies [25,26]. Prior to HIFU treatment, ultrasound localization is required to assess the safety of the patient’s acoustic channel and the accessibility of the treatment target area to determine the treatment regimen. Gastrointestinal preparation is required the day before HIFU treatment, similar to the preparation before colonoscopy. To minimize skin damage caused by HIFU, the treatment area should be shaved and moisturized on the day of surgery. The patient is given general anesthesia by a qualified anesthesiologist. During treatment, ultrasound can be used to detect the distance between the treated lesion and the edge of the lesion and the surrounding vulnerable structures (eg, the intestinal and biliary stents) in real time to prevent complications caused by heat. The power of HIFU ablation will be adjusted in real time according to the treatment.

If a patient has multiple liver metastases, HIFU ablation should not be performed on more than 3 lesions at once to ensure patient safety and tolerance. If there are more than 3 liver metastases, it is possible to ablate the largest 3 first, monitor the remaining lesions, and ablate them again if necessary.

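### The safety set requires an injection, so a patient who starts HIFU but never receives PD-1 blockade is left out of the safety results

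*Protocol article*

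**What the plan says.** The Statistical Analysis section of the protocol article defines the safety population as "All patients who are injected with a minimum of 1 dose of the research medication and have a minimum of 1 safety report". The two conditions are joined by *and*, so both must be met. No other safety population is described, and *safety report* is not defined.

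The Intervention section makes both components the trial treatment: "Eligible patients will receive HIFU on liver metastases and PD-1 blockade therapy". It also shows which of them is injected: "The PD-1 blockade was injected repeatedly every 3 weeks for 6 cycles". On timing, the abstract's Methods paragraph states: "The treatment regimen involves administering HIFU to liver metastases 1 week before the first dose". The Intervention section gives the interval but not the order: "ablation of metastatic liver lesions was planned to take place within no more than 7 days of immunotherapy". The Focused Ultrasound Ablation section adds that "The patient is given general anesthesia by a qualified anesthesiologist", and it foresees heat complications near vulnerable structures.

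The objective in the abstract is "to investigate the effectiveness and safety of HIFU in combination with immunotherapy for lung cancer with liver metastases", and the End Points section lists safety as a secondary end point. That section has adverse events recorded during therapy and up to 28 days after the last dose.

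**The concern.** Membership of a safety set should follow from exposure to the trial treatment. Here it follows from exposure to the second component only. HIFU comes first, and it is what the trial adds to a PD-1 regimen that the Intervention section calls standard. If a HIFU or anesthetic complication prevents the first injection, the patient fails the injection condition and neither the patient nor the event appears in the safety results. The exclusion can thus depend on the outcome being measured, and in a trial of 30 patients one or two such cases would change the reported rate visibly.

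The second condition has a different weakness. Requiring a safety report makes the denominator depend on whether data exist. How much that matters turns on what a report is.

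**Working it through.** The article states no figure that depends on the safety set: no expected adverse event rate, no number treated with HIFU but not injected, no number without a report. There is nothing to reproduce. The check is a reading of the text, followed by an illustration with assumed counts.

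**Reading of the text**

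1. Condition A is at least one injected dose of the research medication. The article does not expressly equate research medication with PD-1 blockade, but PD-1 blockade is the only injected trial treatment it names, and HIFU is not an injection.
2. By the abstract, HIFU precedes the first PD-1 dose by 1 week. The Intervention section's limit of 7 days is compatible with that. Its remark that the combination is given once in week 1 does not close the gap, because HIFU may still come first.
3. It follows that:
   - HIFU started, later injected, report present: in the set, including any harm from HIFU.
   - HIFU started, never injected: out of the set, whatever happened.
   - Injected, no safety report: out of the set (condition B).

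**Illustration 1: never-injected patients**

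The planned number, 30, is from the Statistical Analysis section; all 30 are assumed to start HIFU. With *e* patients who have an event, of whom *k* are never injected:

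- rate in all treated = *e*/30
- rate in the stated safety set = (*e* − *k*)/(30 − *k*)

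| Assumed *e* | All treated | *k* = 1 | *k* = 2 | *k* = 3 |
|---|---|---|---|---|
| 3 | 3/30 = 10.0% | 2/29 = 6.9% | 1/28 = 3.6% | 0/27 = 0% |
| 5 | 5/30 = 16.7% | 4/29 = 13.8% | 3/28 = 10.7% | 2/27 = 7.4% |

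The limiting case *e* = *k* = 2, with Clopper-Pearson 95% intervals:

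- All treated: 2/30 = 6.7%, interval 0.8% to 22.1%.
- Stated safety set: 0/28 = 0%, upper limit 1 − 0.025^(1/28) = 12.3%.

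**Illustration 2: the report condition**

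If a report means an adverse event record, and *m* injected, event-free patients have none, the rate becomes *e*/(30 − *m*). With *e* = 5, 5/30 = 16.7% becomes 5/29 = 17.2%, 5/28 = 17.9%, 5/27 = 18.5% or 5/25 = 20.0% for *m* = 1, 2, 3 or 5. If a report means any safety assessment after a dose, *m* is likely to be small and the effect slight.

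**The case against.** The strongest reply has four parts.

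- **The gap is narrow.** It is at most a week, and a complication that only delays the injection removes nobody. This stands. A reader might infer that everyone harmed by HIFU before the first injection is lost; the definition does not say that. The loss is confined to patients never injected, and the documents do not say how many there would be.
- **The safety-report wording may be harmless.** The article is condensed, and a definition may sit in the full protocol or analysis plan. This stands in part. A reader might infer that the denominator is wrong in both directions. The text does not establish the upward bias, which needs the reading of a report as an adverse event record. What remains is that the condition is stated and makes the denominator depend on data.
- **The events are recorded and overseen anyway.** HIFU is part of the intervention, events during therapy are recorded, and the Monitoring section provides an independent annual review and a monitoring committee. This is right as far as capture and oversight go, and nothing shows that such events would be concealed from oversight. But recording an event does not put a never-injected patient into the analysis set. The 28-day follow-up is also tied to a last dose, which that patient may not have.
- **Nothing decisive rests on the safety set.** Safety is a descriptive secondary end point; the two-stage rule uses response alone. This stands and limits the weight of the point.

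The reply that the article merely omits detail does not succeed. The injection condition is written out, and no other section of the article widens it.

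**Conclusion.** The point holds within limits. As written, a patient who starts HIFU and is never injected is outside the safety analysis, and this can understate procedural harm in a trial that has the safety of the combination as an objective. The report condition is a second, lesser fault: a safety denominator should not depend on having data, and the direction and size of any bias depend on an undefined term.

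The size cannot be derived from the documents. The counts above are assumptions, and the 0/28 case further assumes that every HIFU complication falls in a never-injected patient. The conclusion also rests on reading research medication as PD-1 blockade and on the order given in the abstract. The definition should be corrected, but it threatens neither the primary end point nor the go/no-go decision.

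**What to change.** Replace the definition with one based on exposure: the safety set is all patients who start any study treatment, meaning HIFU (including its anesthesia) or PD-1 blockade. Drop the safety-report condition. State that adverse events are counted from the start of HIFU, and give a follow-up window for patients who have no PD-1 dose to count from. Showing events before and after the first PD-1 dose separately would help the reader but is optional.

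The cost is a sentence or two. Recording during therapy should already cover events from HIFU onward; only follow-up of never-injected patients might need added collection. No sample size, test or decision rule changes. With 6 participants recruited by April 2024 and results expected in December 2026, the article's timetable allows the change before analysis.
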